#### Endpoints of the pilot study

Eligibility rate: proportion of all eligible patients out of all screened patients. Consent rate: Proportion of consenting patients among all eligible patients. Patient motivation for participation based on a participation questionnaire. Overall accrual per month and adherence to the randomized FU schedule.

Meeting the targets will confirm the feasibility of moving forward with the main trial. If any challenges arise in recruitment, retention, or data quality, insights from the pilot phase are used to adjust and optimize the approach.

### Study procedure

#### Participants and recruitment

Inclusion criteria.

Participants must be aged 18 or older, have a histopathologically proven invasive HNSCC at clinical/radiological stage II–IV (non-surgically treated) or pathological stage II–IV (surgically treated, excluding M1) according to the Union for International Cancer Control (UICC) tumor, node, metastasis (TNM) UICC/TNM 8 th edition. Other inclusion criteria are curative treatment intent, planned FU at the study center, radiological and clinical confirmation of complete remission, and agreement for 5-year FU. Furthermore, signed, written informed consent is required.

Exclusion criteria.

Participants with initial clinical stage I and/or M1 HNSCC, nasopharyngeal cancer or carcinoma of unknown primary, previously treated head and neck cancer (except specified cases), other synchronous or metachronous malignancies (except specified cases), participation in conflicting studies, pregnant or breastfeeding women, and those with conditions affecting protocol compliance will be excluded [46].

For detailed criteria and procedures, refer to the full protocol submitted as supplementary material (see Additional file 1: DeintensiF-Full Protocol).

#### Recruitment procedure

Patients receive study information through a recruitment flyer and complete a participation questionnaire from the treating centers. Patient registration and randomization are performed online in secuTrial®, with eligibility checks and signed consent obtained.

#### Randomization and stratification

Following the entry of baseline information and eligibility criteria, participants will be randomized in secuTrial®. They will be assigned to either the experimental (individualized deintensified FU) or control (conventional FU) arm in a 1:1 ratio. Stratification is done via probabilistic minimization to balance prognostic factors across arms [47, 48]. Stratification factors include tumor stage, treatment modality and trial site.

#### Study intervention

Patients in the experimental arm will have scheduled outpatient visits every 6 months including a clinical examination. In-between, patients complete a monitoring questionnaire monthly, with alerts triggering additional visits, if necessary. Details of the instrument are shown in Table 2. Participants will receive reminders to complete the PROs questionnaire the day before the expected date with up to three reminders in the main study, if missed. During the pilot study, phone calls are conducted if the PROs questionnaire is completely or partially missing 1 day after the planned date, which mimics the automated alert by the app in the future main study. In the main trial, a phone call will also follow 3 days after the app’s notification, in case the questionnaire is still not completed. Patients not able to adequately use the app will be offered a paper-based version of the PROs questionnaire, similar to the pilot study. The use of a paper-based PRO questionnaire in the pilot study is a logistical choice intended to simulate the future electronic alert system. This change is solely for feasibility assessment, and any potential differences in data collection methods will be controlled in subsequent subgroup analyses. If a patient fails to complete the PRO, up to two calls are made within 1 week to gather the results. Depending on the rating, the PRO will trigger an alert, manually by phone call during the pilot phase or automatically through an electronic alert in the main study. The alert will recommend an earlier control visit if the patient’s conditions indicate a possible REC/SPM, with the center scheduling an “open urgent appointment” within 2 weeks.

**Table 2 Tab2:**
[figure not shown]
Patient reported outcome questionnaire (symptom tracker)

Patients in the control arm will have scheduled outpatient visits with clinical examination every 3 months (years 1–3) and every 6 months (years 4–5). In addition, patients will undergo scheduled imaging 6 and 18 months after enrollment. Smokers will have additional chest CT-scans 30, 42, and 60 months after enrollment. In the conventional arm, participants will also complete the PROs questionnaire monthly and during every visit, but neither participant calls will be made nor alerts will be sent.

#### Detailed study procedure

The timing of FU visits and the assessments for participants in both arms (conventional FU and individualized deintensified FU) are outlined in Table 3.

**Table 3 Tab3:**
[figure not shown]
Study assessment schedule

Participants will undergo comprehensive imaging, including head and neck MRI or CT scans and contrast-enhanced trunk CT scans, at 3 to 6 months, and at 6 and 18 months post-randomization, to confirm remission and detect secondary primary malignancies (SPM). Annual low-dose chest CT scans without contrast will be performed on current or recent heavy smokers from 18 months to 5 years, per National Comprehensive Cancer Network (NCCN) Guidelines [13, 24]. Adverse events will be monitored using Common Terminology Criteria for Adverse Events (CTCAE) v.5.0. Medical interactions, including unscheduled visits and supportive treatments, will be recorded via a Concomitant Care Questionnaire. Compliance with FU visits and symptom monitoring using paper or electronic PRO questionnaires will be tracked. Health care utilization costs, including FU visits, imaging, and personnel expenses, will be documented.

#### Fear of REC assessment

Fear of REC is assessed monthly using a single-item screening question developed by Rogers et al. (2015) [49], which rates fear on a scale from 0 to 4 [50]. The English version was translated and back translated to German following European Organisation for Research and Treatment of Cancer (EORTC) standards achieving consensus on the final version.

#### Diagnostic work-up for PRO-triggered visits

For visits triggered by PRO alerts or self-referral, diagnostic work-up follows center standards to assess REC/SPM and/or adverse events. These visits are documented as concomitant care events.

#### Study procedures beyond scheduled FU visits

##### Pilot phase

Participants will fill out a paper PRO form monthly. The study team will call monthly to collect PRO data, offering up to three reminders and further training, if needed. They will advise earlier visits for suspected REC/SPM with the center arranging these within 2 weeks.

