#### Secondary objective

The secondary objective is to investigate adherence to the two FU strategies, defined as the completion of scheduled visits and exams as planned, along with regular recording of signs and symptoms in the patient-reported outcomes (PRO) questionnaire. Good compliance is defined as the realization of the planned/organized visits and exams at the planned time ± 4 weeks as well as regularly recording of signs and symptoms in the PRO questionnaire. A retention target of 90% is set for those completing scheduled FU assessments, alongside an adherence goal of 85% to the FU schedule. To ensure the reliability of the findings, at least 95% completeness is aimed in required data fields, with data audits conducted by the Clinical Trials Unit at the University of Bern.

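### The pilot PRO call procedure is stated in incompatible ways; if only the experimental arm is called, PRO completion cannot be compared between arms as unaided compliance

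*Protocol article*

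**What the plan says.** Study intervention sets out the experimental arm. In the pilot, "phone calls are conducted if the PROs questionnaire is completely or partially missing 1 day after the planned date". The article presents this call as a stand-in for a later feature of the trial, one "which mimics the automated alert by the app in the future main study". Later in the same section comes a maximum: "If a patient fails to complete the PRO, up to two calls are made within 1 week to gather the results". That sentence does not name a phase. The section also gives "up to three reminders in the main study, if missed", so the number three is attached there to the main study. The main study will in addition have a phone call three days after the app's notification if the form is still outstanding.

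The Pilot phase paragraph, under Study procedures beyond scheduled FU visits, reads: "The study team will call monthly to collect PRO data, offering up to three reminders and further training, if needed". Its subject is participants in general. It goes on to have the team advise earlier visits when recurrence or a second primary is suspected. The paragraph after it, on the main study, does separate the two groups when it deals with alerts.

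For the control arm, the text after Table 2 has patients complete the same questionnaire monthly and at visits, but "neither participant calls will be made nor alerts will be sent".

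Background and rationale and Secondary objective define good compliance, for both strategies, as visits and examinations within four weeks of the planned time "as well as regularly recording of signs and symptoms in the PRO questionnaire". Neither says whether a form obtained through a call counts.

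**The concern.** Sites cannot apply both call procedures, and three sites choosing for themselves may choose differently. Two things are at stake.

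The first is the contrast between the arms. Prompting by telephone and advice to come earlier are what the experimental arm adds between visits. A site that follows the Pilot phase paragraph as written would deliver both to control patients. According to Statistical analysis, pilot endpoint data enter the main analysis if the study proceeds, so any such contamination would be carried forward.

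The second is the meaning of the PRO component of adherence. Adherence is the pilot's secondary objective, and Trial design makes progression depend on enrolment and on adherence to the follow-up protocol. If one arm is called and the other is not, the same patient behaviour produces different recorded completion. The size of the difference depends on which call rule a site used.

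**Working it through.** **Step 1. The statements side by side.** The article gives no figure for PRO completion, so there is none to reproduce.

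| Feature | Study intervention | Pilot phase | Consistent? |
|---|---|---|---|
| Trigger | form wholly or partly missing at day +1 | every month, no condition | no |
| Contacts | up to two calls in a week; three reminders tied to the main study | monthly call plus up to three reminders | no |
| Arm | experimental only; control excluded | none named | not if read literally |

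**Step 2. What each reading implies.** Under Study intervention, forms completed before any call can be told apart from later ones, provided the date and mode are recorded. Under the Pilot phase paragraph, the call is itself the means of collection, so that separation is not readily available. If the paragraph covers both arms, it contradicts the control-arm text directly.

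**Step 3. Illustration of the effect on recorded completion.** Let p be completion without a call, q the recovery per call and k the maximum number of calls. Both p and q are assumed, and calls are taken as independent. Then completion = 1 − (1 − p)(1 − q)^k.

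With p = 0.60 and q = 0.50:
- k = 0: 0.60
- k = 2: 1 − 0.40 × 0.25 = 0.90
- k = 3: 1 − 0.40 × 0.125 = 0.95

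Over p = 0.50 to 0.85 and q = 0.30 to 0.70:
- k = 2: from 1 − 0.50 × 0.49 = 0.755 to 1 − 0.15 × 0.09 = 0.987
- k = 3: from 1 − 0.50 × 0.343 = 0.829 to 1 − 0.15 × 0.027 = 0.996
- uncalled: 0.50 to 0.85

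The gap produced by calls alone is (1 − p)(1 − (1 − q)^k). For k = 2 it runs from 0.15 × 0.51 = 0.077 to 0.50 × 0.91 = 0.455, that is, about 8 to 46 percentage points.

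**Step 4. Against 85%, as a yardstick only.** The unaided completion needed to record 85% is 1 − 0.15/(1 − q)^k. With q = 0.30 this is 0.85 for k = 0, 1 − 0.15/0.49 = 0.694 for k = 2, and 1 − 0.15/0.343 = 0.563 for k = 3. Identical behaviour can therefore fall on opposite sides of 85%.

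**Step 5. Precision.** The target is 0.80 × 20 = 16 patients, as stated, so 1:1 allocation gives 8 to 10 per arm. Exact (Clopper-Pearson) 95% intervals are 47% to 100% for 7 of 8 patients and 55% to 100% for 9 of 10, upper limits rounded. A per-arm figure is imprecise whichever rule applies.

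**The case against.** The calls are not a nuisance. They stand in for the app alert and belong to the experimental strategy, and the stated objective is adherence to the two strategies. Completion with calls is a legitimate measure of that. The main trial will also use reminders and a rescue call, so unaided completion alone would probably understate what it will achieve. Both points stand. They rule out two stronger readings that a reader might infer: that recorded PRO adherence reflects the calls rather than the patients, and that the adherence goal should count only forms completed before a call.

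The pilot analysis is descriptive, with no between-arm test of PRO completion stated, and main-study adherence is calculated from scheduled visits. The 85% goal is worded for the follow-up schedule, and the traffic-light figure is not shown, so the weight of PRO completion in the progression decision cannot be seen. This also stands and limits the consequence.

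A reader might further infer that monthly collection by telephone makes completion nearly 100% by construction. The text does not support this: participants first fill in a paper form, and an allowance for reminders presupposes non-response. Nor does the article say how the monthly fear-of-recurrence item is collected or plan a pilot comparison of it between arms. Restricting it to self-completed forms would select on response after randomisation.

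Finally, the Pilot phase paragraph may be a loose summary of the conditional rule for the experimental arm, and the full protocol may be precise. That is possible, but the article itself gives a different trigger and a different number of contacts. This is a contradiction in what is printed, not detail left to another document.

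**Conclusion.** The contradiction is certain: the article's statements on pilot calls disagree on the trigger and the number of contacts and, read literally, on the arm. The documents do not show which version is intended.

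If only the experimental arm is called, PRO completion can be read as adherence to each strategy but not compared as unaided patient compliance. The possible gap from calls alone is about 8 to 46 percentage points with up to two calls, under the assumed ranges for unaided completion and recovery per call and with independent calls. These inputs are not in the documents, so the range shows how large the effect could be and is not an estimate.

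Only the PRO component is affected. Visit and examination adherence, and the main study's visit-based adherence, do not depend on these calls. The point should be corrected, but it does not invalidate the pilot's feasibility assessment.

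**What to change.** 1. Reconcile Study intervention (including the control-arm text after Table 2) with the Pilot phase paragraph on when a call is made, how many contacts are allowed and in which arm. The choice is for the sponsor and investigators.
2. Record the mode and date of completion on each PRO form.
3. Report PRO completion before any call and after calls separately, by arm. Keep the call-assisted figure as the measure of adherence to the experimental strategy.
4. Leave the 85% goal as it is. If fear-of-recurrence data are ever restricted to self-completed forms, do so only as a sensitivity analysis.

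The cost is a text correction, one form field and one extra table. The reported pre-call completion figure will be lower than the call-assisted one, and the text should say why.

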##### Main study (ePRO)

Participants will use a monthly ePRO with alerts triggering faster visits for REC/SPM within 2 weeks for the experimental group. The control group will not receive such alerts.

#### Self-referral visits

Additionally, any participant can initiate non-scheduled visits, with centers obliged to accommodate within 2 weeks.

#### Procedure for suspected REC/SPM

When REC/SPM is suspected, centers will follow their protocols for diagnostic work-up, recording all steps in the eCRF.

Post-confirmation a tumor board will outline the treatment approach. FU deviating from the study will conform to center standards, continuing for 5 years or until death. Data on REC/SPM diagnosis, treatment, and participant health status, including last weight, tobacco/alcohol use and symptom scores, will be collected and tracked.

#### Procedure in case of death

The eCRF will record the date and cause of death, distinguishing if it is related to the primary cancer, SPM, treatment, or other causes.

#### Retention and patient involvement strategies

To promote adherence, participants will get a color-coded alarm flyer outlining FU plans and space for future appointments. The flyer serves as a reminder for post-treatment progress and alerts patients to REC/SPM signs, emphasizing the importance of FU compliance and symptom-driven self-referral with quick contact details provided.

#### Training for early detection

Education on recognizing REC/SPM and adverse effects is given to all. The study uses a monthly ePRO (initially paper-based) to monitor symptoms with automated alerts for the experimental group to schedule earlier visits for REC/SPM symptoms and ensure questionnaire completion and adherence.

#### Non-attendance and recall procedures

For unattended appointments, participants will be contacted up to three times before marking “discontinuation of FU scheme” in the eCRF, unless primary endpoint data are obtainable from the family physician. Unconfirmed survival at 5 years will be “Lost to FU”.

#### Discontinuation of FU

##### Discontinuation criteria

Participants can leave the FU study for REC/SPM diagnosis, serious adverse event (SAE), significant medical condition, pregnancy, non-compliance after three recalls or by own request.

##### Status post-discontinuation

Participants leaving the FU scheme, who do not withdraw consent remain in the trial and should follow the centers’ standard FU protocol.

### Statistical analysis

After a 1-year recruitment period, the primary objective assessment will proceed based on participant accrual. A patient motivation questionnaire will be used to optimize enrollment and refine the study design. Adherence will be monitored until the final participant completes the 12-month FU in the second year. Data from the internal pilot phase will inform potential adjustments to the main trial but will not be analyzed separately unless the trial does not advance.

The internal pilot phase sample size is informed by feasibility objectives, including recruitment rates, participant retention, and protocol adherence, which are critical for assessing the study’s viability. Drawing on internal data from the Department of Oto-Rhino-Laryngology, Head and Neck Surgery at Inselspital, Bern University Hospital, the anticipated participant pool aligns with real-world metrics, ensuring a practical recruitment target for the main trial. This sample size allows for robust evaluation of recruitment and adherence metrics without compromising statistical power for the primary endpoint, given that the main trial’s effect measure—5-year restricted mean survival time—has been calibrated based on historical data approximated by a Weibull distribution (shape parameter *a* = 1.18, scale parameter *b* = 10.25), supporting a 5-year RMST of 4.65 years.

While the pilot’s sample size primarily assesses feasibility metrics, it does not account for the interim analysis, designed as non-binding and thus not impacting type I or II error rates. However, feasibility insights from the pilot phase will guide potential adjustments, ensuring that the full study, expected to enroll 550 participants, meets its recruitment and data quality standards.

Data from the internal pilot phase will be analyzed descriptively to assess feasibility metrics, such as recruitment rates and adherence. The participation questionnaire data will undergo descriptive and qualitative analysis to inform potential adjustments to the main trial, particularly in enrollment strategy and patient information. However, endpoint data collected during the pilot will only contribute to the main trial analysis if the study proceeds.

In the main study, analysis sets are defined in line with estimands, including intention-to-treat and two per-protocol sets. The intention-to-treat set will consist of all randomized participants, regardless of protocol violations, while the per-protocol sets will define adherence differently: (a) “while-on-treatment” excludes non-adherence due to medical reasons, and (b) “hypothetical” includes any non-adherence. Adherence will be calculated based on scheduled visits completed within a ± 4-week window, with classification occurring only before REC/SPM occurrence. The main study’s primary endpoint, 5-year restricted mean survival time (RMST), and secondary endpoints will be analyzed using mixed-effects and negative binomial models, with adjustments for competing events [51–55]. A cost and cost-utility analysis will be performed if the trial shows promising non-inferiority results. This analysis will compare the incremental cost-utility ratio of the deintensified versus standard FU, using quality-adjusted life years (QALYs) and standardized healthcare costs.

For detailed procedures and analysis methods, refer to the full protocol submitted as supplementary material (see Additional file 1: DeintensiF-Full Protocol).

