## Background and rationale

Head and neck squamous cell carcinoma (HNSCC) are the 6 th most common type of non-skin cancer [1]. Tobacco, alcohol, and human papillomavirus (HPV) are the main risk factors. Treatment options vary from surgery to radiotherapy (RT), either alone or combined with chemotherapy (CXRT), tailored to cancer site and stage. Early-stage HNSCC (stages I–II, 30% of cases) typically receive single-modality treatment, while advanced cases (stages III–IVA/B, 70% of cases) often necessitate multimodal approaches, such as CXRT or surgery followed by adjuvant (CX)RT. Cure rates for early-stage cancer reach 80–95%, yet locoregional recurrence (REC) affects 50–60% of advanced cases within 2 years, with 20–30% developing distant metastases. Additionally, there is a + 2–4%/year risk of second primary malignancies (SPM), mainly in the lung (60%) and superior aero-digestive tract (20%). HPV-positive oropharyngeal cancer patients exhibit lower REC/SPM risks [2–9]. The 5-year overall survival rates for HNSCC patients treated between 2002 and 2006 averaged 65.9% [10]. Despite treatment successes, patients face treatment-related morbidities, impacting their quality of life (QoL), necessitating comprehensive follow-up (FU) protocols. Curative setting patients’ FU in this population includes treatment response evaluation, REC/SPM detection, management of treatment sequelae, nutritional restoration, and psychosocial support [11]. Unnecessary investigations that may cause morbidity, discomfort, or stress and may add financial burden on the patient need to be avoided. There is neither consensus nor level one evidence on how to ideally achieve these globally accepted FU goals. Guidelines recommend routine clinical visits for head and neck examination, assessing radiation-induced toxicity and functional rehabilitation [12]. Following baseline imaging (magnet resonance imaging (MRI) and computed tomography (CT)) within 3–4 months post-surgery or after definitive CXRT, long-term reimaging until and beyond 5 years in asymptomatic patients remains controversial and unexplored. Within 3–6 months post-CXRT, a hybrid positron emission tomography CT or MRI (PET) is recommended for treatment response assessment and detection of tumor persistence/progression [13]. A chest CT scan should be performed if chest imaging is requested (chest X-ray detects only 33% of intra-thoracic lesions visualized by chest CT) [14]. Existing FU approaches lack consensus, varying in visit frequency, imaging, and duration, as listed in Table 1 [15–25].

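### The printed Weibull parameters give a 5-year RMST of 4.14 years, not the stated 4.65; the two must be reconciled, and the sponsor should confirm which one underlies the 550

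*Protocol article*

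**What the plan says.** All of this is in the protocol article, mainly under Methods, Statistical analysis.

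- The main trial's effect measure, 5-year restricted mean survival time, "has been calibrated based on historical data approximated by a Weibull distribution". The parameters are printed as "shape parameter *a* = 1.18, scale parameter *b* = 10.25".
- The same sentence ends by describing these parameters as "supporting a 5-year RMST of 4.65 years".
- The sentence supports a reassurance about the pilot's size, which is said to allow the feasibility evaluation "without compromising statistical power for the primary endpoint, given that the main trial’s effect measure" was calibrated in this way.
- The main trial is "expected to enroll 550 participants". The article gives no margin, alpha, power, dropout allowance or derivation for that number, and refers to the full protocol for detailed analysis methods.
- The next paragraph of the section names 5-year RMST as the main trial's primary endpoint. Background and rationale gives the hypothesis as non-inferiority.
- Background and rationale also reports a historical survival level: "The 5-year overall survival rates for HNSCC patients treated between 2002 and 2006 averaged 65.9" percent.

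**The concern.** Once shape, scale and horizon are fixed, the RMST of a Weibull curve is fixed too, so one sentence that prints all four numbers can be checked exactly. An RMST of 4.65 years means that on average 0.35 of the 5 years is lost to death. A curve with about 65% alive at 5 years loses much more than that.

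This is the article's only quantitative survival assumption for the main trial's primary endpoint. The survival level sets the variance of restricted survival time, and with it the power of any given sample size at a given margin. If a planning figure for the endpoint is wrong, or belongs to another curve, a reader cannot tell what survival the non-inferiority comparison was planned for. The main trial depends on the pilot's result, so this can still be settled before it starts.

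**Working it through.** **Inputs.** Shape a = 1.18, scale b = 10.25, horizon 5 years, stated RMST 4.65 years, all from Statistical analysis. The unit of b is not printed. I take years, because the RMST is in years.

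**1. Attempt to reproduce 4.65.**

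S(t) = exp(−(t/b)^a), and RMST(5) = ∫₀⁵ S(t) dt.

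- S(5) = exp(−(5/10.25)^1.18) = exp(−0.4287) = 0.651.
- RMST(5) = 4.140 years by numerical integration.
- Letting a run from 1.175 to 1.185 and b from 10.245 to 10.255 gives 4.135 to 4.145.

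The stated figure is not reproduced. The gap is 4.65 − 4.14 = 0.51 years. Mean time lost within 5 years is 5 − 4.14 = 0.86 years, against 5 − 4.65 = 0.35.

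**2. Other readings of the parameters.**

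| Reading | RMST (years) |
|---|---|
| S(t) = exp(−t^a / b) | 3.78 |
| Shape 1/1.18 | 3.77 |
| Exponential, scale 10.25 | 3.96 |
| Shape and scale swapped | 1.12 |
| Scale in months, horizon 60 months | 0.81 |
| S(t) = exp(−b t^a) | 0.13 |
| S(t) = exp(−(bt)^a) | 0.09 |
| Alive at 6 months, next 5 years | 4.08 |
| Alive at 6 months, 5 years from the origin | 4.25 |
| Alive at 6 months, next 5 years plus those 6 months | 4.58 |

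None gives 4.65. Adding a flat half year to 4.14 gives 4.64, but that is a mean over 5.5 years and not a 5-year RMST. With the printed parameters the horizon would have to be 5.82 years to reach 4.65.

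**3. What 4.65 would require.** Solving RMST(5) = 4.65 with one parameter held:

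- shape held at 1.18: scale about 23.5, S(5) = 85.2%;
- scale held at 10.25: shape about 2.06, S(5) = 79.6%.

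**4. Spread of restricted survival time.** SD² = ∫₀⁵ 2t S(t) dt − RMST². For the printed Weibull this is 19.205 − 4.140² = 2.063, so SD = 1.436. The scale refit gives 0.997 and the shape refit 0.872. At a fixed margin the required N is proportional to SD²:

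- (1.436/0.997)² ≈ 2.1;
- (1.436/0.872)² ≈ 2.7.

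**5. Illustration for 550.** My assumptions, none of them stated in the article: 275 per arm, complete follow-up, the same curve in both arms (true equality), one-sided 2.5%. Power = Φ(margin/SE − 1.96) with SE = SD × √(2/275), which is 0.1225 for the printed Weibull and 0.0850 for the scale refit.

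| Margin (years) | Printed Weibull (RMST 4.14) | Scale refit (RMST 4.65) |
|---|---|---|
| 0.20 | 37% | 65% |
| 0.25 | 53% | 84% |
| 0.30 | 69% | 94% |
| 0.35 | 82% | 98% |
| 0.40 | 90% | over 99% |

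The smallest margin with 80% power is (1.96 + 0.84) × SE: 0.34 years for the printed Weibull and 0.24 years for the scale refit.

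**The case against.** The strongest reply is that this is one wrong number in the text and no more. The printed Weibull implies 65.1% survival at 5 years, close to the 65.9% in Background and rationale, so the parameters look coherent. The 4.65 could be a misprint or a figure carried over from another calculation, and 550 could have been computed correctly from the Weibull. This stands as a possibility and cannot be excluded. The closeness to 65.9% is only a plausibility check, because the article does not say that the two come from the same data.

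A second reply is that the article describes a pilot with descriptive feasibility aims, and that the full protocol holds the main trial's sample-size calculation. That is also right: no pilot endpoint or threshold depends on the RMST, and the absence of a margin or a power statement from the article is not a fault. But the contradiction is not a matter of omitted detail. Both numbers are printed, in one sentence, and that sentence is used to reassure the reader about power.

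A reader might go further and infer that the sample size rests on two incompatible survival assumptions, or that 550 is underpowered. The article supports neither. It never derives 550, so whether either figure entered the calculation cannot be seen. Under the printed Weibull alone, 550 would have 82% power at a margin of 0.35 years and 90% at 0.40, given the assumptions above. Nor does 4.65 point to one particular population: survival at 5 years would be about 80% or about 85%, depending on which parameter is changed.

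**Conclusion.** The sentence is wrong as written. A Weibull with shape 1.18 and scale 10.25 has a 5-year RMST of 4.14 years, 0.51 below the stated figure. Neither rounding nor any other parameterisation, unit or conditioning on early survival that was tried removes the gap. This part assumes only that the scale is meant in years, and the reading in months fails as well.

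The consequence for the main trial is open. If 550 was computed from the Weibull, only the text changes. If it was computed from 4.65 and the Weibull is the right description of the patients, the required number at a fixed margin would be about 2.1 to 2.7 times larger than planned for. That range rests on the two single-parameter refits, and the power figures rest on the assumed margins, alpha, complete follow-up and equal arms. They show how sensitive the design is and do not estimate the trial's actual power. The point deserves correction before the main trial proceeds, but it does not undermine the pilot.

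**What to change.** Reconcile the pair in the Statistical analysis section, in one of two ways:

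- state a 5-year RMST of 4.14 years (65% alive at 5 years) for shape 1.18 and scale 10.25; or
- if 4.65 is intended, for instance for patients already in remission 6 months after treatment, give the Weibull parameters and the time origin that produce it.

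Then confirm which of the two the 550 was based on. Repeat the non-inferiority calculation only if it used the wrong one.

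The cost is one integral, a look at the existing sample-size calculation and a corrected sentence. The possible downside is a less favourable power for 550 if the calculation turns out to have used 4.65 and the printed Weibull is the right curve.
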